**Study Coordinating Centre:**

Nottingham Digestive Disease Centre BRU

[name],

Queen’s Medical Centre

Nottingham University Hospitals,

Nottingham,

[name]

SYNOPSIS

| Title | Pilot study: MRI study of Diverticular disease symptoms and its relationship to visceral adipose tissue. |
| --- | --- |
| Acronym | DDOMRI |
| Short title | DD obesity MRI study |
| Chief Investigator | [name] |
| Objectives | To determine differences in adipose deposition and adipokines on diverticular disease symptoms and small bowel water using MRI in participants. |
| Study Configuration | Single centre parallel groups |
| Setting | Secondary care |
| Sample size estimate | No previous studies have used MRI measures of visceral and subcutaneous fat to assess its relationship to symptoms in diverticular disease.  However based on results using abdominal MRI to detect fat distribution by Liou et al in 2006[50], the sample size required to detect a 30% difference in visceral fat between groups with a power of 90% and p<0.05 is 35 participants per group. |
| Number of participants | 105  Expected 500 participants needed to contacted to identify 105 participants for MRI part of study |
| Eligibility criteria | 1. Participants must have symptomatic and asymptomatic Diverticular disease confirmed on endoscopy/ telescope test, barium enema or CT scan   (Symptomatic disease is define as lower abdominal pain >1hr on 3 or more days per month for longer than 3 months.)   1. 18 – 85 years of age. 2. Signed informed consent |
| Description of interventions | Participants will include;   - 1. 35 participants with symptomatic DD and a patient heath questionnaire 15 score of >7   2. 35 participants with symptomatic DD and a patient heath questionnaire 15 score of <7   3. 35 participants with asymptomatic DD   Participants will complete one of each of the following on one occasion: Bowel symptom questionnaires, bowel habit diary, patient heath questionnaire 15, Hospital and Anxiety Depression score questionnaire, McGill pain questionnaire.  Participants will provide 1 stool sample and have a MRI scan of their abdomen and give 20ml of blood from a peripheral vein. |
| Duration of study | 14 days  Recruitment planned for January 2011  Duration of study up to 3 years |
|  |  |
| Outcome measures | Primary End-point  1. Difference in the volume of visceral fat compared to abdominal subcutaneous fat between symptomatic and asymptomatic DD groups  Secondary End-Points. Differences between:   1. Adiponectin and leptin serum levels between symptomatic and asymptomatic DD groups 2. The incidence of diarrhoea between participants with a BMI <25Kgm-2 and those >25Kgm-2. 3. Adiponectin and leptin serum levels between DD groups with and without diarrhoea 4. Small and large bowel water and lumen diameter in symptomatic and asymptomatic DD groups 5. Calprotectin levels between symptomatic and asymptomatic DD groups. 6. Microbiological gut profile between symptomatic and asymptomatic DD groups. |
| Statistical methods | Statistical analysis will carried out with the use of Prism 4 (GraphPad Software Inc, San Diego, CA). Comparisons between groups were performed by using 2-tailed unpaired t test or the Mann–Whitney's U test, for normal and non-normal data respectively. |

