## PRIMARY OBJECTIVE

Difference in the volume of visceral fat compared to abdominal subcutaneous fat between symptomatic and asymptomatic DD groups

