# Methods

## Participant groups

We will recruit n = 35 participants in each group (Total 105). Participants will include;

- 1. 35 participants with symptomatic DD and a patient heath questionnaire 15 score of >7
  2. 35 participants with symptomatic DD and a patient heath questionnaire 15 score of <7
  3. 35 participants with asymptomatic DD

The DD groups will be age and sex matched.

Having excluded those with e.g severe co-morbidity, alcoholism or drug dependence or inability to give informed consent (see exclusion criteria), we will invite participation in the MRI study day.

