# STATISTICS

### Methods

Statistical analysis will carried out with the use of Prism 4 (GraphPad Software Inc, San Diego, CA). Comparisons between groups were performed by using 2-tailed unpaired *t* test or the Mann–Whitney's *U* test, for normal and non-normal data respectively by [name] and [name]

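### The primary test is picked on normality alone, which gives no protection against unequal spread if the contrast is 70 symptomatic vs 35 asymptomatic participants

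*Protocol*

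**What the plan says.** The Synopsis (Statistical methods) states: "Comparisons between groups were performed by using 2-tailed unpaired t test or the" Mann–Whitney U test. The STATISTICS section (Methods) repeats the rule and gives the same sole basis for choosing: "for normal and non-normal data respectively". Neither place mentions the spread of the groups or says whether the t test assumes equal variances.

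The PRIMARY OBJECTIVE is a two-level contrast: "Difference in the volume of visceral fat compared to abdominal subcutaneous fat between symptomatic and asymptomatic DD groups".

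The section on participant groups recruits three groups: "35 participants with symptomatic DD and a patient heath questionnaire 15 score of >7", "35 participants with symptomatic DD and a patient heath questionnaire 15 score of <7" and "35 participants with asymptomatic DD". The total is 105. Sample size and justification gives 35 per group to detect a 30% difference in visceral fat with 90% power at p<0.05. It cites an earlier abdominal MRI study and states no SD.

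**The concern.** A two-level endpoint, three groups of 35 and only two-sample tests most naturally give 70 vs 35. With equal group sizes the pooled-variance t test tolerates unequal variances well. At 2:1 it does not: if the larger group is the more variable its standard error is too large, and if the smaller group is the more variable it is too small. The rule asks only about normality, so it cannot detect this, and its alternative, Mann–Whitney, is also sensitive to unequal spread at unequal sizes.

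At stake are the calibration of the primary p value and some power. The Protocol's first hypothesis links a higher proportion of visceral fat to more symptoms. If the symptomatic group has more visceral fat, and spread rises with the mean, the larger group is the more variable and the cost is mainly lost power.

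**Working it through.** **Inputs.** From the Protocol: 35 + 35 symptomatic, 35 asymptomatic, 30% difference, 90% power, p<0.05, two-tailed test. Assumed, because the Protocol gives no SD: the ratio r = SD(asymptomatic)/SD(symptomatic) and the coefficient of variation (CV). The t test is taken as the pooled-variance form and the two symptomatic groups as pooled.

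**1. The Protocol's own figure.** With n = 35 per group, the detectable standardised difference is d = (1.960 + 1.282) × √(2/35) = 0.775, or 0.786 by the t distribution. A 30% difference then implies CV = 0.30/0.786 = 0.38. A CV of 0.30 would need 23 per group and 0.50 would need 60. The stated 35 can be neither confirmed nor refuted; it is consistent with a CV of about 38%. With equal SDs and the same d, 70 vs 35 has about 96% power.

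**2. Type I error of the pooled t test, large-sample formula.** Set SD(symptomatic) = 1.
- Variance that the test uses: V_p = [(69 + 34r²)/103] × (1/70 + 1/35)
- True variance: V_t = 1/70 + r²/35
- Error ≈ 2 × [1 − Φ(1.983 × √(V_p/V_t))]

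At r = 0.67: V_p = 0.0351, V_t = 0.0271, 1.983 × 1.137 = 2.255, error 2.4%.
At r = 1.5: V_p = 0.0605, V_t = 0.0786, 1.983 × 0.878 = 1.741, error 8.2%.
At r = 2: V_p = 0.0853, V_t = 0.1286, 1.983 × 0.815 = 1.615, error 10.6%.

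**3. Simulation, normal data with equal means, 70 vs 35.**

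| r | Pooled t | Mann–Whitney | Welch |
|---|---|---|---|
| 0.5 | 1.7% | 3.4% | 5.1% |
| 0.67 | 2.6% | 3.7% | 5.0% |
| 0.77 | 3.3% | 3.9% | 4.9% |
| 1 | 4.9% | 4.8% | 4.9% |
| 1.3 | 7.2% | 6.3% | 5.1% |
| 1.5 | 8.6% | 7.0% | 5.1% |
| 2 | 11.0% | 8–9% | 5.2% |

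Repeat runs agree to within about half a percentage point.

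**4. The normality rule.** Mann–Whitney was used when a normality test gave p<0.05 in either group, and the pooled t test otherwise. The Protocol does not say how normality is judged, so this form is an assumption. On normal data the rule gives 2.8% at r = 0.67, 8.3% at r = 1.5 and 11.1% at r = 2, so it offers no protection.

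**5. Equal sizes.** At 35 vs 35, V_p and V_t are both (1 + r²)/35, so the distortion cancels. Simulation gives 4.8% to 5.1% for the pooled t test and 4.8% to 5.9% for Mann–Whitney over the same r.

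**6. Power in the more plausible direction.** Take means 1.3 (symptomatic) and 1.0 (asymptomatic) with the same CV, so r = 1/1.3 = 0.77. At CV 38% the SDs are 0.494 and 0.38.
- True SE = √(0.494²/70 + 0.38²/35) = 0.0872
- Pooled SE = √{[(69 × 0.494² + 34 × 0.38²)/103] × (1/70 + 1/35)} = 0.0951
- Pooled t: Φ[(0.30 − 1.983 × 0.0951)/0.0872] = Φ(1.28) = 90%
- Welch: critical value about 1.99, Φ(0.30/0.0872 − 1.99) = Φ(1.45) = 93%

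At CV 50% the same steps give 67% and 73%. Most of that shortfall from 90% comes from the larger CV, not from the test.

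**The case against.** Several stronger readings are tempting, and the Protocol does not support them.

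- **That it prescribes an equal-variance test.** It says only that the t test is unpaired. Welch's test is also unpaired, and a separate analysis plan could name it. Pooled variance is the usual reading, not a stated one.
- **That the contrast is fixed at 70 vs 35.** Pooling is an inference, and the sample size is justified at 35 per group. Under pairwise comparisons the t-test part falls away (step 5).
- **That false positives of 9% to 11% are to be expected.** These need the asymptomatic group to be 1.5 to 2 times as variable, and no figure or argument in the Protocol points that way. Spread that merely rises with the mean is equal when the means are equal, so it leaves type I error near 5% and matters only for power. Mixing two PHQ-15 strata widens the symptomatic group, which is the conservative direction, and only mildly. Reaching r = 0.67 by mixing alone needs strata about 2.2 SD apart: 1 + 2.2²/4 ≈ 1/0.67².
- **That a Mann–Whitney result cannot be set against the 30% target.** An estimate can be reported beside it, and the test holds 5% for its own null of identical distributions.
- **That a log scale is required.** How visceral fat is to be compared with subcutaneous fat is not defined. A visceral-minus-subcutaneous difference can be negative and cannot be logged.

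It is also fair to say that this is a pilot and that 90% power at the implied CV meets the stated target. What remains is that the Protocol itself states the selection rule, and normality is its only criterion. On no reading does that criterion guard against unequal spread at 2:1 sizes.

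**Conclusion.** The point holds in a limited form. If the symptomatic groups are pooled, the t test is the pooled-variance form and the spreads differ, neither branch of the rule holds 5%. In the direction that the study's hypothesis makes more plausible, the pooled t test is conservative (2.6% to 3.3% at SD ratios 0.67 to 0.77) and costs about 3 points of power at CV 38%. The inflated figures mark the edge of an assumed range and are not a prediction. Welch's test stays at 4.9% to 5.2% on normal data throughout. On log-normal data with equal means it gave 5.0% to 6.2%. The size of the effect rests wholly on assumed SD ratios and CVs. This is a modest weakness with a very cheap remedy.

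**What to change.** State the primary contrast explicitly: 70 vs 35 if the two symptomatic groups are pooled, or the pairwise comparisons if they are not. For the primary endpoint, in both the Synopsis (Statistical methods) and STATISTICS (Methods), replace the choice based on normality with a prespecified Welch unequal-variance t test, reporting the difference with a 95% confidence interval. Keep Mann–Whitney as a sensitivity analysis. A log scale with a ratio of geometric means is optional. It applies only if the endpoint metric is strictly positive, such as visceral volume or the visceral/subcutaneous ratio.

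The cost is a sentence or two of wording and no extra data. With equal spreads Welch has the same size as the pooled t test (4.9% each at r = 1).

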# ABBREVIATIONS

|  |  |
| --- | --- |
| AE | Adverse Event |
| BRU | Biomedical Research Unit |
| CI | Chief Investigator overall |
|  |  |
| CRF | Case Report Form |
| DD | Diverticular Disease |
| DAP | Data Analysis Plan |
| DMC | Data Monitoring Committee |
|  |  |
|  |  |
| GCP | Good Clinical Practice |
| HDL | High density lipoprotein |
|  |  |
| IBS | Irritable Bowel Syndrome |
| ICF | Informed Consent Form |
| IL | Interleukin |
|  |  |
| NDDC | Nottingham Digestive Disease Centre |
| NHS | National Health Service |
|  |  |
| P/GIS | Parent / Guardian Information Sheet |
| PI | Principal Investigator at a local centre |
| PIS | Participant Information Sheet |
|  |  |
| REC | Research Ethics Committee |
| R&D | Research and Development department |
|  |  |
|  |  |
|  |  |
|  |  |
|  |  |
|  |  |
|  |  |
|  |  |

# STUDY BACKGROUND INFORMATION AND RATIONALE

## Diverticular disease

Colonic diverticulosis is the most common structural abnormality of the colon, yet our understanding of it is rudimentary. It affects 5% of people in their 5th decade and up to 66% of the elderly population in the United Kingdom[1]. It is responsible for substantial morbidity with 68,000 hospital admissions recorded per year in the UK and it contributes to about 2,000 deaths.

The definitions of diverticulosis and diverticular disease were established by the European Association for Endoscopic Surgery consensus development meeting in 1999[2]:

“Colonic diverticular disease is a condition seen mostly in the sigmoid region. It is characterized structurally by mucosal herniation through the colonic wall, generally accompanied by muscular thickening, elastosis of the taenia coli, and mucosal folding. This condition may be asymptomatic (*diverticulosis*) or associated with “symptoms,” termed *diverticular disease,* which may be complicated or uncomplicated. The term *diverticulitis* is used to indicate superadded inflammation involving the bowel wall. Other pathologic complications include perforation, fistula, obstruction, and bleeding.”

Studies using national databases of hospital admissions suggest its incidence and/or complications are increasing. A recent study from the United States reported a 26% increase in admission for acute diverticulitis between 1998 and 2005. The rise in admission rates were greatest in younger patients e.g. 45-64 years and 18-44 years[3].

**Obesity and Gastrointestinal disease**

Increasing evidence suggests a link between obesity and gastrointestinal dysfunction and disease. Abdominal pain, bloating and diarrhoea have been correlated with a BMI >25kg/m2 from population based studies[4-7]. Decreased colonic compliance and pain sensation has also been associated with a BMI >25Kg/m2 [8]. Other supportive evidence includes a noticed decrease in the incidence of reported gastrointestinal symptoms with increased exercise and healthy diets (high fruit and fibre)[9]. However, different eating patterns between obese and lean individuals does not fully explain the effect of BMI on reported gastrointestinal symptoms[10].

In a recent scintigraphic gastrointestinal transit study of 287 IBS patients (118 C-IBS, 139 D-IBS, 30 M-IBS) and 170 healthy volunteers, colonic filling and transit were measured at 6, 8, 24 and 48hrs. The researchers found that transit measured at 8, 24 and 48hrs showed statistical difference, especially those with a BMI >30Kg/m2 when adjusted for age, gender and subject types[11]. The reasons underlying the association between obesity and altered colonic transit are not known, but may include:

1. Overwhelming of the jejunal absorption by a high carbohydrate and fat loaded diet, resulting in a higher osmotic chyme being passed distally, with retention of water content.
2. Increased bile acid excretion leading to cholerrheic diarrhoea as a high BMI has been associated with a greater incidence of idiopathic bile acid malabsorption compared to normal weight individuals[12].

The influence of adipose tissue on gastrointestinal immunological and hormonal function may also play a role[13, 14].

**Obesity and Diverticular disease**

There is increasing evidence that obesity is linked to complications of diverticular disease. In Parks’ 1968 study of colonic specimen, 50% of DD samples had excess fat attached compared to control samples with no noticeable gender difference[15].

More recent epidemiological studies have also suggested an association. In a 5 year retrospective study of 61 patients with diverticulosis, a significant difference in body mass index (BMI) was demonstrated between those with no symptoms and those who developed perforation or recurrent episodes of diverticulitis[16]. In a larger prospective cohort study, a BMI >30kg/m2, high waist circumference and a high waist to hip ratio was shown to significantly increase the relative risk of diverticular bleeding and diverticulitis[17]. Studies of patients under the age of 40yrs with acute diverticulitis have also demonstrated an association with obesity[18]. In addition a correlation between obesity and uncomplicated symptomatic diverticular disease has been found in a Nottingham study[19]

With the prevalence of obesity increasing in westernised populations, the risk of complications from diverticular disease is likely to increase as well. However there is little understanding of how obesity increases diverticular complications.

**Possible mechanisms linking obesity to symptomatic diverticular disease**

1. **Association with lifestyle risk factors**

It has been speculated that the increase in incidence of diverticular disease and its complications[3], may be linked to changing western lifestyle. Western diets, especially the lack of cellulose in the diet, and decreased mobility increase the risk of developing diverticular symptoms[20, 21]. As these are linked with the development of obesity, a high BMI may be a surrogate marker for other lifestyle factors that predispose to diverticular complications. Obesity has also been linked to other gastrointestinal pathologies[22-24], including colorectal carcinoma[24-26], chronic inflammation[25, 27] and changes in gastrointestinal microflora.

1. **Inflammation**

Visceral fat has secretes systemic factors that influences on metabolic, endocrine and immunological functions. Visceral fat can also have local influences upon the organs it surrounds, in a paracrine manner. Adipocytes secrete a variety of important compounds:

1. **Adipokines and cytokines**
   1. **Adiponectin**

Adiponectin is produced from adipocytes [28, 29]. Adiponectin is inversely related to BMI and its levels are greater in women than men[24]. Low adiponectin levels and higher concentrations of cytokines, e.g. TNF alpha, IL6, IL8, IL10 and IL1beta, are thought to be involved in the development of insulin resistance and possibly insulin growth factor(IGF) and IGF binding proteins 1 and 2[24].

Adiponectin also has anti-angiogenic and anti-inflammatory effects. Deficient mice have more severe form of chemically induced colitis that normal mice[30, 31]. Variations in adiponectin concentrations have also been reported in UC and Crohn’s disease (CD). Adiponectin and leptin have been shown to be up-regulated in CD compared to visceral fat samples from colon cancer or diverticular disease patients[32].

- 1. **Leptin**

Leptin is an adipocyte specific hormone. It acts on appetite and bodyweight and circulating levels have been associated with colonic cancer. It has similar effect on oesophageal and colonic cell lines, increasing angiogenesis, cell proliferation and metalloproteinase expression.

Leptin levels correlate with white adipose fat mass and is coded for by the obese (ob) gene, while its receptor is coded by the diabetes (db) gene. Levels are greater in women than men, even when adjusted for by BMI. It has multiple actions in satiety and inflammation (see figures from Lago et al 2007[33]).

It acts on a variety of immunological cells such as monocytes, neutrophiles, basophils, NK cells and T cells. In T cells it effects the activation and balance between TH1 and TH2 cytokine production, causing a pro-inflammatory TH1 response. Leptin is itself increased by mediators of inflammation such as lipopolysaccharide (LPS), IL-1 and IL-6. Knockout mouse models suggest leptin is important in development of inflammatory diseases, such as colitis. However its exact mechanism is not fully understood[33].

Leptin has been identified as a critical component in the development of tactile allodynia in a partial sciatic nerve ligation (PSNL) mouse model of pain. After PSNL, adipocytes around the epineurioum increased expression of leptin. Mice given antibodies against leptin and leptin knockout mice failed to produce allodynia, which was reverse after administration of leptin. It is thought that leptin acts by attracting Macrophages, with leptin receptors to injured nerves and caused production of pro-nociceptive mediators Leptin induces iNOS, COX-2 and MMP-9 via phosphorylated signal transducers and activators of transcription 3 (pSTAT3) pathways, which up-regulate the expression of leptin[34]. Peritoneal administration of leptin has also been found to cause pain in mice models[35].

In clinical studies, individual levels of adipokines from synovial fluid, from arthritic knees undergoing joint replacements, did not correlate well with pain scores. However adioponectin-leptin ratios were significantly correlated with pain scores from the Short form McGillPain questionnaire[36]. Waist circumference, BMI and female sex have also been found to be predictive of leptin levels in synovial fluid[37]. Leptin has also been suggested to play a role in endometriosis patients with chronic pelvic pain[38]. From Lago et al 2007[33].

1. **Inflammatory cells**

Adipose macrophage numbers is associated with degree of an individual’s adiposity. They are attracted from the peripheral circulation by monocyte chemoattractant protein 1 (MCP-1) and TNF alpha or from pre-adipocyte differentiation. These cells are thought to influence cytokine production and insulin resistance. There is speculation that the type of macrophage e.g. type 1 ‘classically activated’ or type 2 ‘alternatively activated’, may also be influenced by obesity. Type 2 macrophages are activated by IL4 or/and 13 and secrete IL-10, suppressing adaptive immunity, and allowing tissue remodelling and promoting tumour development and progression[24].

## Altered bowel habit and diverticular disease

Persistent or intermittent alteration of bowel habit is a common complaint in patients with diverticulosis and diverticular disease. A recent study suggests that 28.5% of patients with diverticulosis have altered bowel habit[39] and 16.5% frequent lower abdominal pain. Diverticular patients often complain of constipation (11.7% functional and 18.4% chronic) and/or diarrhoea (6.4% functional and 12.2% chronic)[39]. This is especially the case in the over 65yrs age group there is a correlation between diarrhoea predominant IBS (OR 1.9 95% CI 1.1 - 3.3 P 0.02) and mixed IBS (OR 3.0 95%CI 1.2 - 7.4 P 0.02) and diverticulosis[39].

## Causes of alteration in bowel habit in diverticular disease

The cause of altered bowel habit in IBS and DD is not well understood. In IBS animal models, electrophysiological and bio-molecular studies suggest a long term interaction of the immune system and the visceral nervous system[40]. Changes in micro-organisms within the gastrointestinal tract may also contribute to the maintenance of an altered immune system and are thought to play a role in symptomatic diverticular disease[41] and post-infectious IBS[42].

Genetic techniques for micro-organism profiling have recently been used in IBS. Differences in flora have been identified in diarrhoea predominant IBS (D-IBS)[43, 44]. Increased prevalence of Proteobacteria and Firmicutes and a reduction of Actinobacteria and Bacteroidetes species have been found in D-IBS samples compared to controls[43]. The interaction between the gastro-intestinal flora, immune system and the visceral nervous system has been implicated in a number of functional and inflammatory gastrointestinal diseases[45]. In DD, Diverticular associated colitis and bacterial overgrowth have also been blamed[46].

Therefore, the causes of constipation, diarrhoea or mixed picture of diverticular disease and IBS are probably multi-factorial and include changes in small bowel and colonic dysmotility, mucosal inflammation and intestinal microflora.

